## List of Abbreviations:

|       |                                                      |
|-------|------------------------------------------------------|
| ACQ   | Asthma Control Questionnaire                         |
| AQLQ  | Asthma related Quality of Life Questionnaire         |
| CIS   | Checklist individual strength                        |
| CRC   | Clinical Research Collaboration                      |
| DPIA  | Data Privacy Impact Analysis                         |
| eCRF  | electronic Case Report Form                          |
| ERS   | European Respiratory Society                         |
| HCI   | Health Care Utilization                              |
| SAQ   | Severe asthma questionnaire                          |
| SHARP | Severe Heterogeneous Asthma Registry Patient-centred |
| WPAI  | Work Productivity and Activity Impairment            |
| GCP   | Good clinical practice                               |

# 1. Overview/summary

## Protocol Title:

SHARP CENTRAL registry

## Type of Study

Prospective and retrospective real-life observational study

## Steering committee:

See Appendix 2

## Study centres:

Contributing study sites throughout Europe

## Study period

Prospective, open-ended study. Study participants are asked at the time of signing up for SHARP CENTRAL Registry (= at the baseline visit) to attend as many annual follow up visits as possible

## Study objectives

- To collect retrospective and prospective data on the phenotypical characteristics of patients with severe asthma, treatment strategies and patient responses to treatment, burden of severe asthma across Europe at baseline and during follow-up.
- To obtain natural history data on a wide spectrum of severe asthma patients
- To expedite identification and recruitment of participants for clinical trials
- To plan for future research studies (observational and interventional trials aimed at better symptom control and improving quality of life).

## Study population

Study participants will be adults with diagnosis of severe asthma according to international guidelines. All study participants must be able to provide informed consent.

## Study design

At the baseline study visit, patients will sign an informed consent form, and clinical data from the patient's medical files that are listed in appendix 1 will be collected and entered in the eCRF. Patients will also be asked to complete 6 questionnaires related to asthma.

At each annual follow up study visit, identical data to the ones at the baseline visit will be collected.

## Number of subjects

This study will include as many eligible subjects as willing to participate. We hope to recruit at least 30 patients with severe asthma per 1,000,000 inhabitants residing in each individual country participating in the SHARP CENTRAL Registry within Europe within 6 years.

### Inclusion criteria

All adults with a physician's diagnosis of severe asthma residing in one of the European countries are eligible to participate. Participants may be adult (18+) with no upper age limit, male or female. All participants must be able to provide informed consent for themselves.

### Exclusion criteria

Subjects who are unable to understand the study protocol or unable to give informed consent.

### Assessments and measures

See appendix 1

## 2. Detailed study description

### Background

Asthma is a heterogeneous, inflammatory airway disorder with complex pathophysiological mechanisms (1). Although in most asthma patients the disease can be well controlled with inhaled anti-inflammatory and bronchodilator medications, this treatment fails in about 5-10% of patients (2). These patients develop severe asthma, which is a debilitating disease, associated with frequent severe exacerbations, emergency visits, and hospitalizations, resulting in a poor quality of life. For many years patients with this condition were dependent on the chronic use of high-dose inhaled and oral glucocorticoids, which put them at increased risk for serious and often life-threatening adverse events (3). However, recently, new biologics for severe asthma have become available (4). These biologics target key cytokines of so called "Type 2" airway inflammation, interleukin(IL)-4, IL-5 and IL-13. Mepolizumab and Reslizumab bind to interleukin (IL)-5, Benralizumab binds to the IL-5 receptor, while Dupilumab binds to the alpha subunit of the IL-4 receptor, thereby blocking IL4 and IL13 signalling. Treatments with these biologics have already resulted in remarkable improvements of asthma symptoms and quality of life, although, for reasons that are not understood, not everyone benefits despite meeting the approved inclusion criteria (4). However, many questions about the natural history, burden and costs of severe asthma, disease mechanisms, identification of different phenotypes, prediction of therapy response remain unanswered (5). These questions will be answered in studies organized by the ERS SHARP CRC, using data from SHARP CENTRAL Registry as well as other, already established, registries of patients with severe asthma in Europe.

### Summary of Published Information

The past two decades have seen the creation of several European collaborations focusing on severe asthma, beginning in the late 90s with the Framework Programme (FP)-4 funded project on severe asthma, the European Network For Understanding Mechanisms Of Severe Asthma (ENFUMOSA), a cross-sectional observational study which provided the proof of principle for large collaborations (6). Soon after, a more in-depth project was established, focusing on mechanisms and biomarkers of severe asthma: Longitudinal Assessment of Clinical Course and BIOMarkers in Severe Chronic AIRway Disease (BIOAIR) project, funded by the FP-5 and FP-6

and several national funding bodies (7). More recently, the Unbiased BIOMarkers in PREDiction of respiratory disease outcomes (U-BIOPRED) programme, funded by the EU Innovative Medicines Initiative (IMI) project, sought to provide a step-change in phenotyping of chronic airways disease through the use of multi-dimensional clinical outcomes, 'omics biomarkers and sophisticated lung imaging (8). The shared ambition of all these projects was to improve the definition of airways disease phenotypes in order to enable better targeting of existing drugs and those in development and to improve the understanding of determinants of disease severity, disease progression and risk of exacerbations. These collaborations have produced more than 60 high impact publications in respiratory journals and numerous communications at international meetings. The concept of phenotype and endotypes, defined by shared clinical and underlying mechanistic features, respectively, is accepted both in respect of mechanisms and selection for treatment with biologics, for example anti-IL-5 antibody for eosinophilic forms of asthma (9).

During the same period, individual countries have also established national consortia, recognizing their essential role in bringing together the expertise that exists in individual centres and that this also brings people with asthma together. Some have focused on asthma and others have covered a spectrum of lung diseases: the Netherlands Severe Asthma Research Network, the British Thoracic Society Difficult Asthma Registry, the Belgian Severe Asthma Registry (10) the Spanish collaboration for asthma, the German Center for Lung Research, Poland's Polastma (National Programme of Early Diagnosis and Therapy of Asthma (11)), the Finnish National Asthma Programme (12) and the United Kingdom's National Institutes for Health Research (NIHR) Translational Research Collaborations in Inflammatory Respiratory Disease (TRC), all supported by various national public funding schemes. Several studies have shown that biomedical research which is carried out through international and interdisciplinary collaboration is of significantly higher quality and impact than research performed by a single centre or discipline. Thus, the national programmes in Finland, Poland and the UK (11,12,13) focusing on management and education, have resulted in marked improvements in clinical outcomes, showing the value of collaborative effort.

ERS SHARP CRC was conceived as a long-term project with the following mission (14): a) to gather essential information about the clinical and scientific expertise, existing capabilities and supporting infrastructure in centres across Europe, b) create a registry of people with severe asthma called SHARP CENTRAL registry and integrate it with other severe asthma registries in Europe, c) undertake research of relevance to people with severe asthma that can be best done through large collaborations.

ERS SHARP CRC builds on strong collaborative relationships among basic scientists, clinical investigators and patient organisations for severe asthma in the context of the European Respiratory Society. ERS SHARP CRC was reviewed and approved by the ERS Research Council, is sponsored by the ERS and receives additional funding from 5 pharmaceutical companies (GlaxoSmithKline, Sanofi, Chiesi, Novartis and TEVA).

## Rationale

As severe refractory asthma is a relatively rare condition (15), no single study site is in the position to obtain clinical data in sufficient numbers to conduct conclusive studies concerning the majority of questions of clinical and patient relevance in real life severe asthma. Therefore, a cooperative effort throughout Europe appears an appealing avenue to provide large enough clinical data sets to answer questions conclusively by conducting sufficiently powered studies. Data from SHARP CENTRAL registry, being the central data registry of ERS SHARP CRC should assist in answering questions about (amongst others) the natural history of severe asthma, its burden and costs, underlying disease mechanisms, different phenotypes, prediction of therapy response, using independent real life data sets.

## Objectives

### *Primary Objective*

SHARP CENTRAL Registry is the central registry of ERS SHARP CRC and primarily designed to collect prospective data on the phenotypical characteristics of patients with severe asthma, treatment strategies and patient responses to treatment, burden of severe asthma across Europe at baseline and during follow-up.

### *Secondary Objectives*

- To obtain natural history data on a wide spectrum of severe asthma patients
- To expedite identification and recruitment of participants for clinical trials
- To plan for future research studies (observational and interventional trials aimed at better symptom control and improving quality of life).

Research projects should aim to advance scientific knowledge towards optimizing treatment strategies that reduce the burden and costs of severe asthma, improve patients quality of life, and prevent poor outcomes.

The SHARP CENTRAL Registry database containing pseudo-anonymized data will be de-identified and integrated with other anonymized European severe asthma databases via a data integration platform controlled by the SHARP CRC. Data will be used for a variety of different analyses, which may be broadly categorized as either cross-sectional analyses or longitudinal analyses. SHARP CENTRAL Registry places no limit on the sample size to be collected or a timeframe in which the study will be completed. It is intended that data will be collected as long as needed to respond to pending questions defined by the SHARP CRC. The gradual amassing of phenotypical data will result in cumulative increases in statistical power in order to continuously improve the assessment tools that monitor the course of severe asthma and to identify clinical predictors of therapeutic responses, adverse events and patient relevant outcomes.

## Participant Selection

### *Inclusion Criteria*

SHARP CENTRAL Registry concerns adult patients ( $\geq 18$  years) with severe asthma in the Europe. Severe asthma is defined according to international ERS/ATS guidelines (16). Briefly, this includes all adult asthma patients with uncontrolled symptoms for at least 6 months despite treatment with medium/high doses of inhaled corticosteroids, with or without oral corticosteroids, in combination with at least one other controller medication (e.g. long acting beta-2-agonists, theophylline), and having been checked for adherence to the medications, inhalation technique and co-morbid factors. These patients qualify for additional treatments for severe asthma, such as biologics. Some patients will already be using these therapies. Patients must be capable of giving informed consent and be able to travel to office/hospital for study visits.

### *Exclusion Criteria*

Patients with alcohol/substance abuse within the past 6 months, or serious mental illness that might preclude subject's ability to comply with treatment will be excluded.

## Consent Procedures

After speaking with a qualified nurse, physician or researcher who has provided an overview of the registry, if interested, the patient will be given a copy of the patient information sheet and the informed consent form to review. Study participants will be offered two levels of consent: a) to enter the registry for research purposes, and b) to allow future contact for invitation to participate in additional research studies. Additionally, patient contact information will be collected to facilitate future communication.

The patient will be informed that their participation in the registry is voluntary and will not in any way change their relationship with their own treating physician. Sufficient time (which may differ between European countries) for review of the patient information sheet and the informed consent paperwork will be given to allow the patient to request answers to any questions about the registry they may have. The patients will receive the contact information on who they can contact about these questions.

The informed consent form will then be signed by the patient or the legal representative and the person obtaining informed consent. The patient will be provided a copy of the signed and dated consent.

## Registry Procedures

### *Specific Training*

The research registry study team and all other persons assisting with the registry will be adequately trained about the protocol, the registry procedures, and their duties and functions.

### *Recruitment of participants*

Patients contacting the asthma clinic to schedule an appointment for evaluation of their (severe) asthma will be informed about the registry and will be given the option to participate. When the patient comes to the clinic for their visit, information regarding registry participation will be provided by a qualified research staff member. This oral information will be provided while the patient is in a secluded area where confidentiality is guaranteed.

### *Data Collection Schedule*

All data points collected for the registry will be collected as part of the asthma clinic. Investigators will be asked to evaluate participants at least once a year. The study calls for the documentation of annual assessments, with predefined range of tolerance of  $\pm 1$  month.

### *Enrolment*

Prior to the initial visit, the patient will be consented. Initial baseline demographics of age, gender and ethnicity will be collected from clinic records. Medical history will be collected from clinic records and patient interview. Data from physical examination, diagnostic tests, and current medication use will be taken from clinic records. Patients will be asked to complete 6 questionnaires during clinic visits.

Subsequent yearly appointments: vital signs, height, weight, BMI, pulmonary function tests and current medications will be collected. The study subjects will be asked to complete 6 questionnaires either at the clinic, at home or digitally. All additional registry data (e.g. diagnostic tests) will be collected according to standard of care.

If and when the SHARP CRC develops additional questionnaires or diagnostic tests, these will be added but the patient will have the right to opt out of these and continue with only the original set of questionnaires and diagnostic tests.

## Registry Duration

Patients will remain active in the registry until they voluntary withdraw or expire. Registry enrolment will be ongoing.

## Registry Infrastructure

SHARP CENTRAL Registry will use an already existing electronic health record infrastructure designed for disease monitoring (CASTOR EDC). Castor EDC is a secure, cloud-based data solution, enabling researchers to easily capture and integrate data from any source. Thousands of medical device, biotech, and academic researchers around the world are using Castor EDC (Electronic Data Capture) to accelerate their studies. More information can be obtained from <https://www.castoredc.com>. Within SHARP CENTRAL Registry each participating country will have its separate databases. Institutes and user accounts for data-entry will be created within each country-specific database so that research workers have only access to records of their own site.

In addition, data can be directly obtained from patients using online questionnaires with e-health devices that can be connected with CASTOR EDC and are compliant with relevant regulations, such as GDPR and ISO 27001. An e-health system that is under development for that purpose is the PatientCoach system of the Leiden University Medical Center in The Netherlands.

## Materials of Human Origin: Collection, Preparation, Handling and Shipping

The current projects conducted by the SHARP CRC do not include any collection of samples at individual sites for centralised analysis but if and when projects that do require additional samples, these will be handled according to standard good clinical practice (GCP) principles.

## Data Management and Quality Plan

### *Data De-identification, Confidentiality, Storage, and Retention*

Participant data are entered into the eCRF after creating a unique pseudonym for each participant. The pseudonym will consist of the first 3 letters of the country, 3 letters of the institute plus an automatically generated serial number. The identifying information will be stored in a secure place and be only accessible to the primary investigator of the individual participating centre. This person will only access the identifying information in case of medical urgency. The identifying information will never be stored electronically.

Registry documentation and paperwork will be stored at the asthma clinic in a locked file cabinet. Registry records will be retained as long as required by GCP rules in each country” after the completion of the registry. After that period of time, all individual patient information will be shredded.

In order to make the data from SHARP CENTRAL Registry available for analysis the country-specific databases containing pseudo-anonymized data will be exported, anonymised and merged into a single datafile that can be used with standard statistical software packages. For integration with other anonymized European severe asthma databases a SHARP CENTRAL MySQL database, containing the merged tables, will be hosted at the Leiden University Medical Center. This MySQL database will allow connection with the data integration platform controlled by the SHARP CRC. This platform allows mapping of the SHARP CENTRAL Registry database to the OMOP (Observational Medical Outcomes Partnership) Common Data Model (CDM) which will form the basis for federated analyses based on SHARP CENTRAL Registry and other anonymized European severe asthma registries. OMOP is supported by the OHDSI collaborative framework ([www.ohdsi.com](http://www.ohdsi.com)). OHDSI provides resources to convert a wide variety of datasets into the CDM, as well as a plethora of tools to take advantage of the data once it is in CDM format. This includes Atlas a web based, open source software tool for researchers to conduct scientific analyses on standardized observational data.

### *Data Quality*

The data entry forms in CastorEDC contain questions with coded answer categories (check boxes and radio-groups) where possible and input fields for quantitative data with plausible range checks and alerts. Quality control procedures for this research register will also include remote control visits. This means that source data will be verified by randomly selecting register participant

records, and comparing data from the original patient file with data in the electronic database record. If errors are common, data will be completely checked prior to data analysis.

### *Data Sharing*

The study participant will give informed consent to his/her hospital and SHARP CENTRAL Foundation. The hospital will be responsible for obtaining the informed consent.

SHARP CENTRAL foundation and the hospital will be jointly responsible for the data. They will conclude a Data Sharing Agreement.

### **Sample Size Determination**

SHARP CENTRAL registry places no limit on the overall sample size to be collected. However, each project that will be carried out with data from the SHARP CENTRAL Registry defining a specific-read out or endpoint will include a sample size calculation and – if appropriate – a power analysis specific to the objectives of the study.

### **Registry Data Points**

Initial baseline demographics of age, gender and ethnicity will be collected from clinic records. Medical history (age of asthma onset, hospital admissions, ICU admissions, co-morbidities) will be collected from clinic records and patient interview.

Data from physical examination (height, length, blood tests, sputum tests, skin prick tests, pulmonary function test, Chest X-ray, Chest CT, DEXA scan, bronchoscopy, medication use will be taken from clinic records.

Questionnaires: Asthma control questionnaire (ACQ) (17), Severe asthma questionnaire (SAQ) (22).

Additional Questionnaires that are set up for the project “SAQ-Burden of Asthma” and that could potentially be added for future SHARP studies:

Asthma quality of life questionnaire (AQLQ) (18), Work productivity and activity impairment (WPAI) (19), Health care utilization (HCI) (20), Checklist individual strength (CIS) (21).

The questionnaires will be completed by the patient either at the clinic, at home or by a e-device at least once a year.

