## Forms and data handling

A complete CRF is attached in the Appendix. The data are entered electronically via internet-based technology. The SHARP CENTRAL Registry web-portal is separated into several parts with different access rules. Any given site investigator in SHARP CENTRAL Registry is allowed to see only data on study participants under the care of the study site to which the site investigator is affiliated. SHARP CRC is allowed to view all data of all centres for plausibility checks, quality control and monitoring. The whole database is saved on a server.

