### **[To be completed once every year by patient]**

- ☐ Asthma control questionnaire (ACQ)  
Mean score \_\_\_\_\_

- ☐ Asthma Quality of Life Questionnaire (AQLQ)  
Mean score \_\_\_\_\_
- ☐ Work productivity and Activity Impairment (WPAI)  
Mean score \_\_\_\_\_
- ☐ Health care utilization Questionnaire  
Mean score \_\_\_\_\_
- ☐ Checklist Individual Strength  
Mean score \_\_\_\_\_
- ☐ Severe asthma Questionnaire  
Mean score \_\_\_\_\_

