**[To be completed once every year by case-manager]**

Is patient lost to follow-up?

- ☐ yes
  - ☐ Patient passed away
  - ☐ Patient changed email address
  - ☐ Patient withdrew consent
  - ☐ Other \_\_\_\_\_
- ☐ No

Date of examination (dd-mm-yyyy):

Height: \_\_\_\_\_ cm  
 Weight: \_\_\_\_\_ Kg  
 BMI: \_\_\_\_\_ Kg/m^2

Smoking Status:

- ☐ Never Smoker[SEP]
  - ☐ Ex-Smoker (Quit smoking >12 months)
  - ☐ Current Smoker
- Current number of Pack years: \_\_\_\_\_

Has patient ever been admitted to ICU for asthma?

- ☐ Yes
- ☐ No

If yes, total number of ICU admissions:  
Has patient ever been intubated due to asthma?

- ☐ Yes
- ☐ No

If yes, total number of intubations:

Has the patient ever attended rehabilitation

- ☐ Yes
  - How often? \_\_\_\_\_ times
  - Last time \_\_\_\_\_ years ago
- ☐ No[SEP]
- ☐ Unknown

Has the patient ever undergone bronchial thermoplasty?

- ☐ Yes  
Date/year \_\_\_\_\_
- ☐ No[SEP]
- ☐ Unknown

Has spirometry ever been performed (If done multiple times, please report most current result)[SEP]

- ☐ Yes
- ☐ No

If Yes, when was most recent pulmonary function test performed? (dd/mm/yyyy)

If Yes, which values are available?

- ☐ Pre-bronchodilator values
- ☐ Post-bronchodilator values

|          | PRE
BRONCHODILATOR |                | POST
BRONCHODILATOR |                |
|----------|-----------------------|----------------|------------------------|----------------|
| FEV1     | L                     | %
predicted | L                      | %
predicted |
| FVC      | L                     | %
predicted | L                      | %
predicted |
| FEV1/FVC | %                     |                | %                      |                |

Has exhaled NO testing ever been performed?

- ☐ Yes
- ☐ No

If yes, please report date of most recent result:

FeNO \_\_\_\_\_ppb

Has CO diffusion capacity been performed (ever)?

- ☐ Yes
- ☐ No

If yes, please report date of most recent result:

DLCO: \_\_\_\_\_ mmol/min/kPa and \_\_\_\_\_ % predicted

Has bodyplethysmography (body box) ever been performed?

- ☐ Yes
- ☐ No

If yes, please report date of most recent result:

TLC: \_\_\_\_\_ L and \_\_\_\_\_ % predicted

RV: \_\_\_\_\_ L and \_\_\_\_\_ % predicted

Has bronchial provocation testing with methacholine ever been performed ?

- ☐ Yes
- ☐ No

If yes, please report date of most recent result:

- ☐ Positive (BHR demonstrated, FEV1 decline  $\geq 20\%$ )

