- ☐ Yes, because of (very) good response

☐ No, patient is currently not treated with biologics

Does the patient currently use any of the following (non-pulmonary) medications?

- ☐ Nasal corticosteroids[L][SEP]
- ☐ Antihistamines[L][SEP]
- ☐ Bisphosphonates[L][SEP]
- ☐ Calcium suppletion ( $\pm$  vit D)[L][SEP]
- ☐ Proton pump inhibitors[L][SEP]
- ☐ vit K antagonists[L][SEP]
- ☐ NSAIDs[L][SEP]
- ☐ Other

-----  
-----  
-----

[L][SEP]

Has the patient received one of the following asthma add-on treatments  
IN THE PAST?

☐ omalizumab

If Yes, date of last administration (dd/mm/yyyy)

If yes, reason for stopping?

☐ insufficient reduction of systemic steroid dose[L]SEP

☐ Adverse effects[L]SEP

☐ Insufficient improvement of symptoms or exacerbations[L]SEP

☐ Insufficient improvement of lung function

☐ mepolizumab

If Yes, date of last administration (dd/mm/yyyy)

If yes, reason for stopping?

☐ insufficient reduction of systemic steroid dose[L]SEP

☐ Adverse effects[L]SEP

☐ Insufficient improvement of symptoms or exacerbations[L]SEP

☐ Insufficient improvement of lung function

[L]SEP

☐ reslizumab

If Yes, date of last administration (dd/mm/yyyy)

If yes, reason for stopping?

☐ insufficient reduction of systemic steroid dose[L]SEP

☐ Adverse effects[L]SEP

☐ Insufficient improvement of symptoms or exacerbations[L]SEP

☐ Insufficient improvement of lung function

[L]SEP

☐ benralizumab

If Yes, date of last administration (dd/mm/yyyy)

If yes, reason for stopping?

☐ insufficient reduction of systemic steroid dose[L]SEP

☐ Adverse effects[L]SEP

☐ Insufficient improvement of symptoms or exacerbations[L]SEP

☐ Insufficient improvement of lung function

[L]SEP

☐ dupilumab

If Yes, date of last administration (dd/mm/yyyy)

If yes, reason for stopping?

☐ insufficient reduction of systemic steroid dose[L]SEP

☐ Adverse effects[L]SEP

☐ Insufficient improvement of symptoms or exacerbations[L]SEP

- ☐ Insufficient improvement of lung function

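### The CRF has no count or date field for exacerbations, non-ICU hospital admissions, emergency visits or systemic steroid courses, although the protocol lists hospital admissions as a data point

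*Protocol*

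**What the plan says.** The primary objective (Protocol, Objectives) is to collect prospective data on phenotype and on "treatment strategies and patient responses to treatment, burden of severe asthma across Europe at baseline and during follow-up". The Background section describes the disease as "associated with frequent severe exacerbations, emergency visits, and hospitalizations".

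On what is to be recorded, Registry Data Points says: "Medical history (age of asthma onset, hospital admissions, ICU admissions, co-morbidities) will be collected from clinic records and patient interview". Ward and ICU admissions are thus two separate items.

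Two sections make Appendix 1 the definition of the dataset. Study design says that "clinical data from the patient's medical files that are listed in appendix 1 will be collected and entered in the eCRF", and Forms and data handling says "A complete CRF is attached in the Appendix".

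In Appendix 1, the yearly case-manager part asks "Has patient ever been admitted to ICU for asthma" and then for the total number; intubation is handled in the same way. The yearly patient part lists the "Health care utilization Questionnaire" with one blank for a mean score, as for the other five questionnaires. The list of past add-on treatments offers "Insufficient improvement of symptoms or exacerbations" as one reason for stopping a biologic.

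**The concern.** The body of the protocol names a data point that the form does not hold. The form also lacks counts for the events by which the Background characterises severe asthma. A site can record that a biologic was stopped because exacerbations did not improve enough, yet nowhere can it record how many there were.

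This is not a matter for a later analysis plan. The sections on sample size and statistical analysis leave endpoints and methods to each project, but no project can analyse a variable that was not collected. Enrolment is open-ended, so each year without these fields adds patient-years without event data. Sites might recover some of this from clinic files later. For patients who withdraw, the protocol bars any further collection from their records, so for them the gap would be permanent.

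**Working it through.** No sample size, power or effect estimate is involved. The check is an item-by-item reading of Appendix 1 against the protocol body.

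| Event | Named in the body | Dedicated count or date field | Nearest item in Appendix 1 |
|---|---|---|---|
| Exacerbations | Background | None | Tick-box reason for stopping a past biologic, merged with symptoms |
| Non-ICU hospital admissions | Background; Registry Data Points | None | Utilization questionnaire, as a mean score |
| Emergency visits | Background | None | Utilization questionnaire, as a mean score |
| Systemic steroid courses | Not named as a data point | None | Current maintenance dose; tapering yes/no |

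Dedicated fields: 0 of 4. Of the four, only hospital admissions is expressly promised as a data point.

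**ICU totals.** The form records lifetime ICU admissions and intubations, but the section is completed every year. New events between visits are therefore this year's total minus last year's total. These two rare, extreme events can be followed, but they say nothing about ward admissions.

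**Infections item.** The co-morbidity question on frequent respiratory infections needing antibiotics is categorical. It is not an exacerbation count.

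**Utilization questionnaire.** Its items are not shown. Even if they include admissions and emergency visits, one mean cannot be split back into its parts: two patients whose admission and visit counts are swapped would have the same unweighted mean. Rates by event type cannot be recovered from it.

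**Status of that questionnaire.** Study design and Enrolment each speak of six questionnaires, and Appendix 1 lists six, including this one. Registry Data Points names two as standard (asthma control and severe asthma) and four as set up for a particular project and possible additions for later studies. The total agrees (2 + 4 = 6), but the status does not. On the narrower reading, the utilization questionnaire may not be collected at all.

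**The case against.** The strongest reply is that the registry names no main outcome. A reader might infer that the primary objective cannot be answered, or that the loss of outcome data is complete. The documents do not support that. The objective is to collect data on phenotype, treatment, response and burden, and the Background describes the disease without specifying endpoints. Many yearly fields bear on burden and response:

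- asthma control, quality of life, work impairment and fatigue;
- spirometry, FeNO and blood eosinophils;
- maintenance steroid dose and tapering;
- biologic start date, and whether a change was made for insufficient or good response.

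This stands, and it confines the point to event-based measures. It is weaker on the narrower reading of Registry Data Points, where only the asthma control and severe asthma questionnaires are standard.

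Second, the electronic form may hold more than Appendix 1 shows. The adverse event section requires all adverse events to be entered in the eCRF, yet the appendix has no general adverse event form. The mean-score line is the same for all six questionnaires and may be a template, and the infrastructure section allows online questionnaires linked to the database, so item-level capture is possible. None of this is stated, however, and the protocol calls the appended form complete. It lowers confidence without removing the mismatch.

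Third, no text requires 12-month event counts. That is correct: the choice of window is a recommendation. Recording nights in hospital or splitting the work productivity score may be useful too, but this mismatch does not show a need for either.

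**Conclusion.** The point holds in limited form and should be fixed. The protocol promises hospital admissions, and the form has no field for them outside the ICU. Nor can the form supply counts or rates of exacerbations, emergency visits or steroid courses. Event-based burden and response therefore cannot be estimated from the form as written, while the symptom, quality-of-life, lung-function and maintenance-steroid side of the objective remains open to analysis.

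This rests on two assumptions. The first is that Appendix 1 as seen is the whole form; the pages after it were not available, and the contents list places the investigator appendix there. The second is that the utilization questionnaire is stored as the form shows, as a mean score. If the eCRF already keeps its items and these include admissions and emergency visits, the gap narrows to exacerbations and steroid courses, provided the questionnaire is core.

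**What to change.** 1. Add three counts to the baseline and annual sections of Appendix 1: asthma exacerbations treated with systemic steroids, emergency visits for asthma, and hospital admissions for asthma. At baseline, use the 12 months before entry. At follow-up, use either the previous 12 months or the time since the last visit.
2. Choose one follow-up window for all sites and print it on the form. If visits fall on anniversaries with the stated tolerance of one month either way, consecutive visits can be 12 - 2 = 10 to 12 + 2 = 14 months apart. A fixed 12-month window would then overlap or leave gaps. A since-last-visit count avoids this and takes its person-time from the examination date already on the form.
3. Store the health care utilization questionnaire by item, not as a mean score.
4. Reconcile Registry Data Points with Study design, Enrolment and Appendix 1 on which questionnaires are core.

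The cost is a CRF amendment and a few minutes of extra entry per patient per year. Sites already consult clinic records and interview the patient for medical history. If the eCRF already has these fields, updating Appendix 1 is enough for items 1 to 3.
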